### Study Aims and Hypotheses

This study is designed to empirically test the controversy regarding both the value of intensive, high dosage training as well as the optimal timing for intensive VR/Robotic training in the first 2 months after stroke. We are continuing an ongoing investigation into the effects of intensive task and impairment-based training of the hemiparetic upper limb with a focus on the hand using robotically facilitated rehabilitation interventions presented in virtual environments. The primary aim of this study is to test, at 4 months post-stroke, whether adding intensive VR/Robotic motor training to a patient's standard of care rehabilitation at 5–30 days post-stroke, improves functional outcomes of the hemiparetic hand when compared to initiating the additional VR/Robotic motor training 30–60 days post-stroke; thus testing the concept of optimal timing. Other comparisons include comparing Early VR to dose-matched usual care to test the potential benefits of the high-intensity VR/Robotic intervention. Comparing dose-matched usual care (10 additional hours of standard therapy) to usual care (no additional therapy) will inform about the benefits of increased dosing (Table 1). See controversies elucidated in recent literature (12, 30). We hypothesize that the outcomes will favor the early, high dosage VR/Robotic hand training group when compared to the delayed VR/Robotic training group and dose matched usual care group. The secondary aims will systematically investigate the mechanisms underlying the changes resulting from early timing of training and increased dosing, specifically changes in kinematics, kinetics, patterns of cortical somatotopic reorganization, and brain connectivity. We further hypothesize that the early, high dosage VR/Robotic hand training group will show a larger relative contribution of restored kinematic motor patterns to the overall improvement in motor function and these functional gains will be associated with the expansion of ipsilesional hand cortical somatotopy.

**Table 1 T1:** Comparison groups.

**Group comparisons**	**Intervention period^**+**^**	**Test**
EVR vs. DVR^*^	5–30 vs. 30–60 days	Timing of a VR/robotic intervention
EVR vs. DMUC^**^	5–30 days	VR/Robotic vs. conventional intervention
DMUC vs. UC^***^	5–30 days	Dosing of an intervention

* Early Virtual Reality vs. Delayed Virtual Reality,

** Dose Matched Usual Care,

*** *Usual Care; ^+^Time Post-Stroke*.

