### Measures

There are several types of outcome measures in this study: clinical measures, neurophysiological measures, kinematic/kinetic measures, a measure of daily use of the hemiplegic extremity, and a quality of life measure. For the clinical measures, a therapist blinded to group assignment will perform all outcome assessments. For the EVR and DMUC groups, the measures will be taken immediately prior to intervention (ideally within 72 h), immediately post-intervention (ideally within 72 h), 1 month post-intervention, and 4 and 6 months post-stroke. For the DVR group, there will be an additional measurement taken immediately post-enrollment (ideally within 72 h). For the UC group, the measures will be taken immediately post-enrollment (ideally within 72 h), 2 weeks post the first test, 1 month post the second test and 4 and 6 months post-stroke.

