**Secondary outcomes – neurophysiological**						
TMS - MEP amplitude and extent	Patterns of cortical reorganization	x	x		x	
EEG	Resting state/task-based brain connectivity	x	x	x	x	x

* *ideally within 72 h after Post-test*.

** *The delayed VR group has two PRE tests, one in the hospital and one immediately prior to the delayed VR intervention*.

*Patterns of Corticospinal Reorganization* will be assayed using single-pulse TMS (Magstim Rapid with an AirFilm Coil). Changes in the ipsilesional and contralesional hand cortical territory will be quantified using motor evoked potentials (MEPs) in persons that meet specific safety criteria for TMS. The topographic representation of the following hand and arm muscles will be mapped before and after training and at the three retention time points: first dorsal interosseous [FDI], extensor indicis longus [EI], abductor pollicis brevis [APB], abductor minimi [ADM], flexor digitorum superficialis [FDS], extensor digitorum communis [EDC], flexor carpi radialis (FCR), extensor carpi radialis [ECR], extensor pollicis longus [EPL], and brachioradialis [BR]. To ensure spatial precision we will employ frameless neuronavigation (Brainsight, Rogue Research, Inc.).

A threshold of 50 uV will be used to detect MEPs against background EMG (45). MEP amplitude will be measured as the peak-to-peak amplitude of the EMG signal 20–50 ms after the TMS pulse. In addition, the amplitude of the background EMG will be calculated as the area under the EMG envelope in the 50 ms interval before the TMS pulse where the envelope is generated by filtering the signal with 2nd order Butterworth filter (5–250 Hz band-pass), full-wave rectifying the filtered signal and applying 20 Hz low-pass filter. MEP and background EMG amplitude will be estimated for each muscle and for each stimulation point. MEP amplitudes and coordinates of the stimulation points will be interpolated to a 7 × 7 cm mesh of 5 mm resolution centered on the M1 hotspot using cubic surface interpolation method (46, 47). This will allow comparisons across maps and sessions. The weighted-average location of corticospinal output devoted to a muscle, or center of gravity (COG), is expressed as an MEP-weighted centroid of the cortical representation in the rostral-caudal (COGx) and medial-lateral (COGy) plane using standard equations (45, 48).

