We will use the robust mixed effect model approach to analyze the data. We demonstrated in the past that this analytic approach is robust to detect treatment effects, even with relatively small groups of patients in whom within-group variance occurs with respect to stroke characteristics (56). Test Time (Pre, Post, 1-month post-treatment, 4 months post-stroke, 6 months post-stroke) and Treatment Group (EVR, DVR, DMUC, UC) will be treated as fixed effects in the mixed models. The interaction term between Test Time and Treatment Group will be included. Baseline measurements will be added as a covariate into mixed models for outcome variables. Random intercept will be used to model subject-level variation. Covariance pattern and model selection will be implemented with likelihood-based tests. Contrasts to compare group means will be applied to obtain comparisons between time, and between treatments, with multiplicity adjustment considered. We have an a priori interest in specific Test Time by Treatment Group interaction effects for the EVR-DVR, for the DMUC-UC, and for the EVR-DMUC comparisons. The particular differences we are interested in are Pre vs. Post and Pre vs. second (4 months post stroke) retention assessments. In the case of balanced data and equal variances, we will use the Tukey procedure to test for significant interaction effects, otherwise, Bonferroni correction will be used. In our design, the timing comparison is the difference between EVR and DVR. The dosage comparison is the difference between UC (usual care) and the DMUC (usual care plus 10 additional hours). In addition, we will be able to compare the type of training effect, VR vs. dose-matched usual care (EVR vs. DMUC), where both types of training are delivered in the same time period.

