## Discussion

This study focuses on arm and hand rehabilitation that (1) can be delivered in an inpatient rehabilitation facility during the early period of heightened neuroplasticity using VR/robotic simulations to facilitate the delivery of increased intensity of an intervention, (2) can quantify intensity to distinguish between total therapy time and actual movement time, (3) can specifically target the particular movement deficits that need to be modified, and (4) can incorporate patients with minimal movement. Independent upper extremity function is critically important to restore full independence and reduce the need for costly supportive care. One of the issues that may contribute to less than satisfactory outcomes for the hand (as well as the arm) is the complexity of hand motor control that involves coordination of multiple degrees of freedom. Early hand therapy is often limited when patients have not recovered sufficient motor function to utilize the hemiparetic hand during functional activities. Frequently therapists train compensatory movements using the less affected upper extremity, in an effort to attain maximal independence prior to patient's discharge in the face of the ever-decreasing length of stay in inpatient rehabilitation as part of a stroke care plan. This VR/robotic system is well-suited for the delivery of hand and arm training for more affected patients. Sensory and perceptual affordances provided by the integration of VR and robotics can target the unique hand deficits that one cannot address in real-world therapy (37), and thus possibly allow for functional improvement to move beyond the spontaneous recovery predicted in the literature (62).

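### The planned EVR-DVR Pre-vs-Post contrast compares different stretches of recovery, so it cannot isolate timing with either DVR pre-test

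*Protocol article*

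**What the plan says.** The Statistical Analysis section declares an a priori interest in the Test Time by Treatment Group interaction for three pairs: EVR-DVR, DMUC-UC and EVR-DMUC. For these pairs it says: "The particular differences we are interested in are Pre vs. Post and Pre vs. second (4 months post stroke) retention assessments". It then assigns the timing question to one pair: "In our design, the timing comparison is the difference between EVR and DVR". Table 1 in Study Aims and Hypotheses gives the same purpose for that pair: "Timing of a VR/robotic intervention".

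In the Measures section, the EVR and DMUC visits after the pre-test are "immediately post-intervention (ideally within 72 h), 1 month post-intervention, and 4 and 6 months post-stroke". So Pre, Post and 1 month follow the training, and only 4 and 6 months follow the stroke. DVR has an extra test; the Table 2 footnote says: "The delayed VR group has two PRE tests, one in the hospital and one immediately prior to the delayed VR intervention". Baseline enters the mixed model as a covariate. The article does not say which of the two DVR tests is Pre in the contrast or the baseline covariate.

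**The concern.** EVR training starts 5–30 days after stroke and DVR training 30–60 days after. A Pre-Post change in each arm contains the effect of training plus whatever recovery and usual care produce in that window. The Discussion itself refers to natural recovery when it hopes the system will "allow for functional improvement to move beyond the spontaneous recovery predicted in the literature". If the two windows hold different amounts of background recovery, the EVR-DVR difference in Pre-Post change is not zero even when timing has no effect.

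Randomisation does not remove this, because the imbalance is created by the measurement schedule. A categorical Test Time factor gives visits at different times post-stroke the same label. A baseline covariate equalises neither time since stroke nor interval length. At stake is a planned inference on the trial's main question whose direction depends on an unstated choice of DVR pre-test. The same problem would affect an EVR-DVR contrast at the 1-month visit.

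**Working it through.** **Inputs from the article.** Start windows: EVR day 5–30, DVR day 30–60. Training: one hour per weekday, 10 hours in total, so 10 weekdays or about 14 calendar days. Sample Size: f = 0.42, alpha 0.05, 24 per group for the main planned contrasts.

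**The plan's own figure.** Power is not stated; I assume 80%. For a two-group contrast, the noncentrality is λ = f²N with 1 and N − 2 df.
- N = 48: λ = 0.42² × 48 = 8.47, power 81.3%.
- N = 46: power 79.6%.

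So 24 per group, 96 in all, is reproduced. It was computed for Baseline and 4 months; Post plays no part in it.

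**Windows.** I assume DVR enrollment also falls at day 5–30.

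| Arm and pre-test | Pre | Post | Length |
|---|---|---|---|
| EVR | day 5–30 | day 19–44 | 14 days |
| DVR, later pre-test | day 30–60 | day 44–74 | 14 days |
| DVR, in-hospital pre-test | day 5–30 | day 44–74 | 14 to 69 days |

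The last range runs from 30 − 30 + 14 = 14 to 60 − 5 + 14 = 69 days. At the midpoints it is 45 + 14 − 17.5 = 41.5 days, against 14 for EVR.

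**Direction.** Let S(t) be spontaneous recovery at day t, with EVR start e, DVR start d, and the same training benefit in both arms, so no timing effect.
- Later pre-test: spurious difference = [S(e+14) − S(e)] − [S(d+14) − S(d)]. This is positive, favouring EVR, for any decelerating curve with e < d.
- In-hospital pre-test: spurious difference = [S(e+14) − S(e)] − [S(d+14) − S(e)] = S(e+14) − S(d+14). This is negative, favouring DVR, for any rising curve with e < d.

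Both vanish only where the arms start on the same day, which the windows allow only at day 30.

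**Illustration.** The curve is an assumption, not in the article: S(t) = A(1 − exp(−t/τ)), A = 15, 25 or 35 ARAT points, τ = 14, 28 or 42 days, e = 17.5, d = 45. For A = 25 and τ = 28: S(17.5) = 11.62, S(31.5) = 16.88, S(45) = 19.99, S(59) = 21.96.
- EVR gain: 16.88 − 11.62 = 5.26.
- DVR gain, later pre-test: 21.96 − 19.99 = 1.97. Difference +3.3.
- DVR gain, in-hospital pre-test: 21.96 − 11.62 = 10.34. Difference −5.1.

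Over the nine combinations the spurious difference is +1.3 to +5.4 points with the later pre-test and −1.4 to −7.9 with the in-hospital one.

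**The 4-month contrast under the same curves.** With the in-hospital baseline, both arms span the same period and the spurious difference is 0. With the later pre-test it is S(d) − S(e), here +3.7 to +11.7 points toward EVR.

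**False-positive rate.** Two-sided t test, 24 per arm, 46 df, noncentrality = bias × √(24/2) = bias × √12, with bias in SD of change. The bias sizes are assumed. The right-hand column assumes Bonferroni over three pairs × two differences = six contrasts (0.05/6 = 0.0083).

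| Bias (SD) | Noncentrality | Alpha 0.05 | Alpha 0.0083 |
|---|---|---|---|
| 0.25 | 0.87 | 14% | 4% |
| 0.50 | 1.73 | 40% | 17% |
| 0.75 | 2.60 | 72% | 45% |

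**The case against.** A reader might infer that the trial's primary timing result is confounded or that its sample size is wrong. The article does not support that. The Abstract, the aims and the Sample Size section all place the primary question at 4 months post-stroke, and the contrasts that set N = 96 are Baseline to 4 months. The challenged contrast is a supporting one. That limit stands, on condition that the in-hospital test is the DVR baseline.

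The sentence naming Pre vs. Post covers three pairs together, and the sentence calling EVR-DVR the timing comparison names no visit. An EVR-DVR comparison around training could also be meant as immediate response: the section on robotic kinetic measures states that purpose. This is a fair reading, but the Statistical Analysis section still makes EVR-DVR Pre-Post an a priori interaction and gives the pair no purpose other than timing.

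The upper false-positive rates are not predictions. They rest on an assumed bias, and the plan does specify a multiplicity adjustment, so the unadjusted column overstates the risk if that adjustment covers these contrasts.

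A blanket restriction to 4 and 6 months would not fit the schedule. Robotic measures are taken only around training, the structured subjective assessment only before and directly after it, and Table 2 lists no 6-month TMS visit. The Aim 2 and Aim 3 sections use the same time and group factors but do not themselves name an EVR-DVR Pre-Post contrast. Finally, the DMUC and UC windows are only broadly aligned: DMUC is tested just before its intervention, while UC is tested after enrollment and two weeks later.

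**Conclusion.** The concern holds for the EVR-DVR Pre-vs-Post contrast. Neither DVR pre-test aligns the windows, and the spurious difference changes sign with the choice between them. The direction needs only that recovery is rising and decelerating and that EVR starts before DVR. The size cannot be fixed from the article: about 14–72% false positives for 0.25–0.75 SD at alpha 0.05, or about 4–45% with Bonferroni over six contrasts, are conditional on those assumed values.

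The powered 4-month contrast and N = 96 stand if the in-hospital test is the DVR baseline. If the later pre-test were used, the 4-month contrast would also favour EVR. The article leaves that open, which is the more important reason to settle the baseline.

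**What to change.** In the Statistical Analysis section:
1. Name the in-hospital (enrollment) test as DVR Pre and as the DVR baseline covariate.
2. Base EVR-DVR timing inference on the 4-month post-stroke visit, with 6 months as supporting where the measure is collected then.
3. Take EVR-DVR Pre-vs-Post, and any EVR-DVR 1-month contrast, out of the inferential, multiplicity-adjusted set and report them as descriptive. Apply this to the ARAT and to the Aim 2 and Aim 3 measures that have stroke-anchored visits.
4. Keep measures taken only around training (robotic kinetic measures, structured subjective assessment) as planned, labelled as descriptive of immediate response and not as evidence of a timing effect.
5. Keep Pre-vs-Post for EVR-DMUC and DMUC-UC, whose windows are broadly aligned.

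The cost is analysis wording only: no added visits or patients, and N = 96 is unchanged. The price is the loss of the immediate EVR-DVR comparison as an inferential result.

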#### Primary and Secondary Outcomes – Clinical

Our overall primary outcome measure will be the ARAT score. Additional secondary outcome measures for Aim 1 will be Box and Blocks and the Upper Extremity Fugl-Meyer Assessment, the Patients' Structured Subjective Assessment questionnaire, the EuroQol Five Dimensions Test and the National Institutes of Health Stroke Scale (NIHSS).

#### Secondary Outcomes - Kinematic/Kinetic

For Aim 2 our initial statistical analysis will be applied to the vector of z-normed kinematic measures [Pinch Force Tracking Error, Maximum Pinch Force, Finger Flexion/Extension Tracking Error, Maximum Finger Opening], with fixed effects of Test Time and Treatment Group (EVR, DVR, DMUC and UC). *Post-hoc* comparisons will be analyzed through pre-planned contrasts. Separate analyses will be conducted for each output variable if appropriate. As exploratory analyses, the relationship between multiple output variables will be investigated using multiple-output-stacked mixed effects models.

Grasping of objects of various sizes and shapes will be analyzed (44). The subjects' ability to preshape their hands as it approaches the object to be grasped will be evaluated using support vector machine (SVM)-based classification analyses of the finger joints. Flexion/extension in the metacarpophalangeal and peripheral interphalangeal joints of the fingers plus finger abduction angles will be used as input variables. At each moment during reaching, the classification algorithm will predict which of the objects the subject is grasping in this particular trial. Classification error will be calculated as percent of trials where the algorithm made an incorrect prediction and will serve as an outcome measure, with smaller error values indicating better hand function. In addition to SVM, other classification methods will be investigated (e.g., linear discriminant analysis). The time profiles of the classification errors for grasping with the affected arm will be analyzed longitudinally. The time profiles of the magnitude of this classification error will be analyzed with mixed model analysis with fixed effects of Treatment Group (EVR, DVR, DMUC, UC), Test Time, Condition (either Object Size: Small, Large; or Object Shape: Round, Rectangular, Irregular) and Movement Time (5–95% epochs). Finally, classification error profiles obtained during grasping with the affected arm will be compared with the profiles of the less affected arm.

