*Real-world Reach-Grasp Test* (44) will be used to measure the kinematics of everyday movements involving grasping and manipulating household objects. The goal of this outcome measure is to analyze whether the intervention training transfers to real-world reaching and grasping patterns of inter-finger coordination during pre-shaping of the hand, coordination between hand pre-shaping and transport of the hand to the target, and coordination of upper limb segments. Kinematics of reaching for an object, lifting it from the support, transporting it to a predefined location, and releasing the object will be evaluated.

The Reach-Grasp Test will be administered to the hemiparetic arm at each test point and the non-hemiparetic upper extremity once using an optical motion capture system (Optitrack Prime 13 cameras, Optitrack, USA). *Fifteen* active makers will be placed on each fingertip, metacarpophalangeal, and proximal interphalangeal joints. Additionally, 4 passive markers will be placed on the back of the hand, elbow, shoulder, and sternum. Subjects will be seated at a table with their hips and knees in a 90 degrees position. Their semi-pronated forearm and palm will rest on the table, with the hand positioned midline between the shoulders and 10 cm away from the chest. Test objects will be positioned at subjects' midline 20 cm from the subjects' hand. Subjects will be instructed to reach for an object, lift it from the support, transport it to a predefined location and release the object. Each reach will be repeated up to 10 times based on subject tolerance. OptiTrack motion capture software (Motive) will be used to record the marker coordinates. Hand peak velocity, time to peak velocity and movement smoothness of hand spatial trajectory will be calculated separately for all three sub movements: reaching to object, transporting object, and returning arm back to the starting position. Hand preshaping during reach will be analyzed as a measure of coordination between hand transport and grasp and will be used as a secondary kinematic outcome (44). Five objects include small (1 inch) and large (3 inch) cubes, small (2.5 inch diameter), and large (4.5 inch diameter) circular objects, and a small spray bottle (4 inch height).

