### Sample Size

For Aim 1, the planned primary analysis method is a mixed effect model. The primary outcome measure is the change in ARAT score from baseline evaluated at 4 months post-stroke. The estimated effect size for the interaction term is 0.42 (Cohen's f), and the estimated within-subject correlation is 0.7. For testing the hypothesis of Treatment Group (EVR, DVR, UC, DMUC) ^*^Test Time (Baseline, 4 M post-stroke, 6 M post-stroke) effect, and assuming compound symmetry correlation for within-subject measurements, for significance level 0.05, a total of 84 patients (21 for each group) are needed to detect the overall Treatment Group ^*^ Test Time interaction effect. But for the main planned contrasts, Treatment Group (EVR, DVR) ^*^ Test Time (Baseline, 4 M post-stroke) and Treatment Group (UC, DMUC) ^*^ Test Time (Baseline, 4 M post-stroke), a total of 96 patients (24 for each group) are required to detect the effect size of 0.42 between EVR and DVR or between UC and DMUC over time. Since detecting these contrasts is the main goal of the study, at least 96 subjects, 24 subjects per group, are required. After taking into account subject attrition, our total sample size will be equal to 120. We plan to run an interim analysis and update the sample size when we have recruited 50% of subjects.

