#### Secondary Outcomes - Neurophysiological

For Aim 3, variables will be analyzed with a mixed model, with fixed effects of TEST TIME (Baseline, Post, 1, 4, 6 M), sensorimotor cortex (Ipsilesional, Contralesional), Muscle (Intrinsic, Extrinsic) and Treatment Group (EVR, DVR, DMUC, UC). AREA (size of the cortical surface area in the affected hemisphere where MEPs can be elicited, to be used as an index of focusing of the cortical excitability distribution) will be used as an outcome measure. In addition to group analyses, we will use a Spearman rank order test to correlate individual subject measures of cortical topography (Area/Volume/COG shift, measured by TMS mapping) and clinical measurements of impairment (hand/wrist UEFMA) and function (distal WMFT) across testing time points. In our experience, individual subject data analysis has proven invaluable in understanding the effects of therapy on functional recovery. Non-parametric statistics (Kruskal-Wallis or Mann-Whitney) will be used for variables that fail tests of normality. Alpha level will be set at 0.05. Tukey *post-hoc* tests will be used to investigate significant interactions.

Lesion size and location (cortical/subcortical) will be used for secondary analyses regarding responders/non–responders, etc. (56–58) in which we used theory-based categorization of brain lesions to determine regions associated with better response to stroke rehabilitation, using a mixed-model analysis.

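### The grasp error-profile model names only a patient random intercept for many values per visit, so its Group by Test Time test is valid only if the covariance selection reaches the visit level, which the plan does not say

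*Protocol article*

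**What the plan says.** All references are to the protocol article.

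- **Statistical Analysis** gives the general mixed model: fixed effects of Test Time (five levels), Treatment Group and their interaction, with baseline as a covariate. On dependence it says "Random intercept will be used to model subject-level variation". The next sentence leaves the covariance pattern and model selection to likelihood-based tests. The stated a priori interest is in Test Time by Treatment Group effects for EVR-DVR, DMUC-UC and EVR-DMUC, with a multiplicity adjustment.
- **Secondary Outcomes - Kinematic/Kinetic** (analysis part) scores classification error as a percentage of trials at each moment of the reach. The profiles go into a mixed model with arm, visit, "Condition (either Object Size: Small, Large; or Object Shape: Round, Rectangular, Irregular) and Movement Time (5–95% epochs" as fixed effects. No further random term is named.
- **Secondary Outcomes-Kinematic/Kinetic** (measures part) describes the source of those profiles: "Each reach will be repeated up to 10 times based on subject tolerance". It names hand preshaping as a secondary kinematic outcome.
- **Secondary Outcomes - Neurophysiological** (analysis part) lists, besides Test Time, "sensorimotor cortex (Ipsilesional, Contralesional), Muscle (Intrinsic, Extrinsic) and Treatment Group (EVR, DVR, DMUC, UC". Again no further random term is named. The significance level is given: "Alpha level will be set at 0.05".

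**The concern.** Patients are randomised, so a treatment effect on change over time must be judged against variation between patients in how they change from visit to visit. A patient intercept removes stable differences between patients. It does not remove what all values from one visit share, such as a bad day or a run of poor reaches. For the grasp profiles this sharing is built in, because every epoch of a visit is scored on the same handful of reaches.

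If nothing else in the model carries that dependence, Group by Test Time is tested against the epoch-level residual. Its standard errors are then too small and its denominator degrees of freedom far too many. What is at stake is the mechanism evidence of Aim 2 and, to a lesser degree, Aim 3. A between-arm difference in preshaping could be declared where none exists.

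**Working it through.** **1. The plan's own figures.** The only error-rate and size figures concern the ARAT: "The estimated effect size for the interaction term is 0.42 (Cohen's f), and the estimated within-subject correlation is 0.7"; "for significance level 0.05, a total of 84 patients (21 for each group) are needed"; "a total of 96 patients (24 for each group) are required to detect the effect size of 0.42 between EVR and DVR". Power is not stated, so 80% is assumed. A noncentral F with λ = f²N reproduces both totals:
- Overall: λ = 0.42² × 84 = 14.82, df 6 and 160, power 0.82.
- Two-group contrast: λ = 0.42² × 48 = 8.47, df 1 and 46, power 0.81, so 24 per group and 96 in total.
- 96 / (1 − 0.20) = 120 at an implied 20% attrition.

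The ARAT has one value per visit, so the point below does not touch these figures.

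**2. Inputs for the profile model.**
- From the article: 4 arms, 24 analysed patients per arm, 5 visits, 2 (size) or 3 (shape) conditions.
- Assumed, because the article does not give them: 10 or 19 epochs, so K = 20, 30, 38 or 57 values per visit; and a share s of within-patient variance common to all values of a visit.

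**3. Formula.** With within-patient variance set to 1, the Group by Time mean square has expectation DE = 1 + (K − 1)s under no treatment effect. With a patient intercept only, its error term is almost entirely epoch-level.

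Take K = 38, s = 0.05:
- DE = 1 + 37 × 0.05 = 2.85.
- Degrees of freedom: Group by Time 3 × 4 = 12; patient-by-visit 92 × 4 = 368; epoch level (480 − 1) × 37 = 17,723.
- Pooled error = (368 × 2.85 + 17,723 × 0.95) / 18,091 = 0.99. The expected F is about 2.9, against a 5% critical value of about 1.75.
- Single contrast: 2[1 − Φ(1.96/√2.85)] = 2[1 − Φ(1.16)] = 0.25.

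**4. False-positive rates at nominal 5%, patient intercept only.** The first figure is the overall Group by Time test, from draws of these mean squares. The second is the unadjusted EVR-DVR Pre to 4-month contrast, from the formula.

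| K | s = 2% | s = 4% | s = 5% | s = 10% |
|---|---|---|---|---|
| 20 | 23% / 10% | 46% / 14% | 56% / 16% | 85% / 25% |
| 30 | 35% / 12% | 65% / 18% | 75% / 21% | 95% / 32% |
| 38 | 44% / 14% | 75% / 21% | 84% / 25% | 98% / 37% |
| 57 | 63% / 18% | 89% / 28% | 94% / 31% | 99% / 45% |

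Simulation of full data agrees within its error. At s = 4% it gave 47–91% and 13–29%, and at s = 10% it gave 86–99% and 27–49%. With no visit variance but serial correlation of 0.5 between neighbouring epochs, it gave 79–86% and 22–26%.

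**5. With the right error level.** Using the patient-by-visit mean square, the overall test rejects 4–6.5% in every simulated setting. If a likelihood-ratio test may add a patient-by-visit term, the rate is 4.7–6.2%, and the term is chosen in 100% of grasp runs at s = 4%.

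**6. Aim 3.** Two hemispheres by two muscle groups give K = 4.
- Five visits, patient intercept only: overall about 9% at s = 4%, 11–12% at 5%, 20–21% at 10% and 39% at 20%.
- Contrast at s = 5%: DE = 1.15, about 7–8%.
- Three visits: overall about 9%, 16% and 27% at s = 4%, 10% and 20%.
- If only the affected hemisphere counts (K = 2, s = 5%): DE = 1.05 and the contrast rate is 5.6%.

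The simulations kept baseline as a time level instead of a covariate, which does not change the mechanism.

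**The case against.** The strongest reply is that the plan never says epochs are independent. The random-intercept sentence and the covariance-selection sentence stand next to each other in the general Statistical Analysis section. If the first applies to Aims 2 and 3, so does the second. Step 5 shows that selection works well when the visit-level term is among the candidates. A reader might infer that the plan tests epochs as independent and that false positives are therefore to be expected. The document does not support that: independence is one possible reading, not a stated rule.

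A second reply is that a journal article commonly leaves covariance detail to the analysis plan. That is fair for silence. Here, however, the article fixes the response rows, the fixed effects and the one random effect. Followed literally, that combination is a poor method. Patterns defined across Test Time, the usual candidates, need not reach the visit-within-patient or epoch level.

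Third, the sizes depend on an assumed epoch count and variance share, and the overall F test looks worse than the planned contrasts. Both points stand, which is why ranges and contrasts are shown. Multiplicity adjustment does not cure the problem. For three comparisons under Bonferroni with DE = 2.85, the per-contrast rate is 2[1 − Φ(2.394/1.688)] = 0.16, against an intended 0.017.

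Fourth, Aim 3 is a weak case, and that stands too. Map area is defined for the affected hemisphere, yet both hemispheres are in the model. The number of TMS visits is also unclear: the opening of the neurophysiological measures section and Table 2 give three, while the corticospinal mapping text and the Aim 3 model imply five.

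**Conclusion.** The point holds as a conditional risk. For the grasp profiles, the validity of the between-arm test turns on a choice the article does not state. With a visit-level term available, the overall test rejects at about 5–6%. Without one, it rejects at about 46–99% and the unadjusted EVR-DVR contrast at about 14–45%, for 20 to 57 values per visit and shares of 4–10%. At a 2% share the figures are 23–63% and 10–18%. All rest on assumed epoch counts and variance shares.

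The Aim 3 map-area model has the same weakness at a modest size: about 9–12% overall at a 4–5% share with four values and five visits, and less with only the affected hemisphere. A reader might extend the point to the trial's main conclusion. That is not supported, since the ARAT contributes one value per visit and neither its analysis nor the sample size is affected. This is a worthwhile correction to secondary analyses.

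**What to change.** **Grasp profiles** (Secondary Outcomes - Kinematic/Kinetic), either of:
- Make the between-arm Group by Test Time test on one summary value per patient-visit, for example mean error over 5–95% of the reach, and keep the profile model descriptive. This is the simpler choice.
- Keep the profile model for testing, but include by default a patient-by-visit random effect and within-visit serial correlation across Movement Time, with Kenward-Roger or Satterthwaite degrees of freedom.

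**Map area** (Secondary Outcomes - Neurophysiological): include a patient-by-visit random effect. Say whether one or both hemispheres are analysed, and reconcile the three-visit and five-visit statements for TMS.

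**Cost:** a sentence or two of analysis wording and no new data. Intervals will be wider and fewer secondary results will reach significance.
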